### Sample size justification

2.4

Sample size for this randomized, sham-controlled pilot and feasibility trial was determined in full alignment with the CONSORT 2010 Statement: Extension to Randomized Pilot and Feasibility Trials (Eldridge et al., 2016), and the optimized sample size estimation method for pilot trials with continuous primary outcomes established by Whitehead et al (Whitehead et al., 2016). As an external pilot trial, the core aim of sample size setting is not to power formal hypothesis testing for intervention efficacy, but to generate a sufficiently precise estimate of the standard deviation of our primary outcome (Metformin Symptom Severity Score total score) to inform the design of a future definitive randomized controlled trial. In detail, according to the optimized sample size estimation method for pilot trials established by Whitehead et al., an estimated final sample of 25 evaluable participants per group (after accounting for a 15% attrition rate from the 30 enrolled participants) yields 48 degrees of freedom for variance estimation. This well exceeds the minimum threshold of 20 degrees of freedom recommended in the literature for stable, unbiased variance estimation in pilot research. No formal hypothesis testing for intervention efficacy is planned in this pilot trial. Core feasibility endpoints include: recruitment rate (target ≥8 participants per month), screening failure rate, treatment adherence rate (defined as completing ≥80% of scheduled treatment sessions), attrition rate (estimated at 15% based on published neuromodulation trials in patients with T2DM), and protocol violation rate. Accounting for a 15% attrition rate, the final enrollment target is 60 participants (30 per group) (Whitehead et al., 2016).

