### Statistical methods

2.10

All data will be managed according to GCP guidelines for clinical trials. Two independent researchers will perform double data entry for all variables, including bowel urgency scores, glucose and insulin metabolism markers, serum inflammatory markers, and safety parameters. Cross-verification is mandatory, and the database will be locked without authorization.

Statistical analyses will be performed by blinded biostatisticians using SAS 9.4 and R 4.2.1. Two analysis sets will be applied: the intention-to-treat (ITT) set includes all randomized participants, and the per-protocol (PP) set includes participants completing ≥80% of the treatment course without major protocol violations, for sensitivity analysis.

Baseline characteristics will be summarized by group. Continuous variables are assessed for normality using the Shapiro–Wilk test: normally distributed variables are presented as mean ± SD, non-normal as median [IQR]; variance homogeneity is assessed via Levene's test. Categorical variables are expressed as counts (*n*) and percentages (%). Between-group comparisons: independent *t*-test or Mann–Whitney *U*-test for continuous variables, Pearson χ^2^ or Fisher's exact test for categorical variables.

Primary and continuous outcome variables (bowel urgency score, FBG, PG2h, FINS, C-peptide, HOMA-IR, ISI, GA, serum IL-6/IL-10/TNF-α, GLP-1, 5-HT, D-lactate, diamine oxidase, and fecal bile acids) will be analyzed using linear mixed-effects models (fixed effects: group, time, interaction; random effect: participant), reporting least-squares means with 95% *CI*. The exact mathematical formulas and covariance structures for these linear mixed-effects models will be fully reported in the final trial publication. Categorical outcomes are analyzed via χ^2^ or Fisher's exact test.

A Multiple Imputation (MI) model will be used as the primary method for missing data. The imputation model will include all primary and secondary outcomes, plus baseline covariates (age, sex, duration of diabetes, baseline metformin dose, baseline Metformin Symptom Severity Score score), with 20 Markov Chain Monte Carlo iterations to generate 20 imputed datasets. The pre-specified linear mixed-effects model will be performed on each dataset, with results pooled via Rubin's rules (Heymans and Twisk, 2022).

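### The stated imputation model omits randomised arm and takes in every outcome at once, so followed as written it shrinks the effect-size estimate and can inflate its standard error

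*Protocol article*

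**What the plan says.** Section 2.10 (Statistical methods) gives imputation the leading role: "A Multiple Imputation (MI) model will be used as the primary method for missing data". It then sets out the contents of the model: "The imputation model will include all primary and secondary outcomes, plus baseline covariates (age, sex, duration of diabetes, baseline metformin dose", closing with "baseline Metformin Symptom Severity Score score), with 20 Markov Chain Monte Carlo iterations to generate 20 imputed datasets". Neither the randomised group nor separate imputation by group is mentioned.

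The model fitted to each imputed dataset is a linear mixed model with "fixed effects: group, time, interaction; random effect: participant", pooled by Rubin's rules. Complete-case analysis is the sensitivity analysis.

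On size, Section 2.4 states that "the final enrollment target is 60 participants (30 per group") with "attrition rate (estimated at 15% based on published neuromodulation trials in patients with T2DM"), leaving "an estimated final sample of 25 evaluable participants per group". It also says that no formal efficacy testing is planned and that the core aim is a precise standard deviation for the primary score. The Discussion paragraph of the Abstract adds effect-size estimates for confirmatory trials to what the pilot will deliver.

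**The concern.** An imputation model should carry at least the structure of the analysis that follows it. Here the analysis estimates a difference between arms, but the stated imputation variables do not identify the arm. A participant with no follow-up would be filled in from a distribution that mixes both arms, so the imputed values contribute no treatment difference. The pooled contrast then moves toward zero.

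The second fault is size. All primary and secondary outcomes enter together, including HOMA-IR and ISI, which Section 2.7.3.3 defines from FBG and FINS. With 60 participants, such a model spends most of its information on estimating itself, and the imputed values become noisy.

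At stake is the effect-size estimate, with its interval, that the pilot is meant to hand to a later trial.

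**Working it through.** **The plan's own figures.** 25 / 0.85 = 29.4, rounded up to 30 per arm, so 60 in total. Degrees of freedom: 2 × 25 − 2 = 48. Both reproduce. (The 48 variables below match this figure only by coincidence.)

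**Attenuation by algebra.** Inputs: 15% attrition (Section 2.4). Assumed, because the documents give no values: unit SD within arm, effect δ of 0.5 to 0.8 SD, baseline to follow-up correlation 0.5, drop-out completely at random.

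- All follow-up missing: imputed values carry no arm difference, so the share recovered is 1 − 0.15 = 0.85.
- Only Week 4 missing: Week 2 carries some arm information. Without arm, the slope on Week 2 given baseline is b = (c + δ²/4) / (v + δ²/4), where v = 1 − 0.5² = 0.75, c = r − 0.25, and r is the Week 2 to Week 4 correlation. The share recovered is 0.85 + 0.15 × b.
  - r = 0.5, δ = 0.5: b = 0.3125 / 0.8125 = 0.385, recovered 0.908.
  - r = 0.5, δ = 0.8: b = 0.41 / 0.91 = 0.451, recovered 0.918.
  - r = 0.625, δ = 0.8: b = 0.535 / 0.91 = 0.588, recovered 0.938.

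The expected loss is therefore 15% when all follow-up is missing and about 6% to 9% when only Week 4 is.

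**Attenuation by simulation** (60 participants, 15% missing, ANCOVA at one follow-up visit as a simple stand-in for the mixed model; mean estimate / true effect, arm omitted):

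| Assumed effect | All follow-up lost | Mixed | Only Week 4 lost |
|---|---|---|---|
| 0.5 SD | 0.82 | 0.88 | 0.91 |
| 0.6 SD | 0.83 to 0.85 | 0.88 | 0.92 to 0.96 |
| 0.8 SD | 0.84 | 0.87 | 0.94 |

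These runs span 0.82 to 0.96, a loss of 4% to 18%. The spread around the algebra is largely simulation error. A longer run (4,000 trials per scenario) gave 0.85 to 0.86 and 0.91 to 0.93 for the two extremes. With arm in the imputation model, all runs returned 0.98 to 1.02.

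**Number of variables.** Visits are taken from Section 2.7, with Table 1 for FBG, PG2h and quality of life:

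- Three visits: symptom score, BSFS, urgency, quality of life, FBG, PG2h: 6 × 3 = 18.
- Two visits: GA, C-peptide, FINS, HOMA-IR, ISI, IL-6, IL-10, TNF-α, GLP-1, bile acids, 5-HT, D-lactate, DAO: 13 × 2 = 26.
- Age, sex, diabetes duration, metformin dose: 4.
- Total: 18 + 26 + 4 = 48.

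Other readings: 30 (post-baseline outcomes 12 + 13, plus 5 covariates), 31 (Table 1 literally: 18 + 2 + 3 + 4 + 4), 45 (no quality of life), 61 (19 outcomes × 3 + 4).

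**Cost in precision** (0.6 SD, auxiliary variables simulated as unrelated to outcome and arm). With 15% missing, 60 × 0.85 = 51 values are observed:

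| Missing | Imputation model | Mean pooled SE | Complete cases |
|---|---|---|---|
| All follow-up | 24 columns, no arm | 0.29 | 0.24 |
| Week 4 only | 43 columns, no arm | 0.44 | 0.25 |
| Week 4 only | 44 columns, with arm | 0.46 | 0.24 |
| Either pattern | 7 to 8 columns, with arm | 0.25 | 0.24 |

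A 43-column regression on 51 values leaves 51 − 43 = 8 residual degrees of freedom. Adding arm cures the bias but not the size.

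**Derived outcomes.** By the protocol's formulas HOMA-IR × ISI = 1/225, a constant, and log HOMA-IR = log FBG + log FINS − log 225. Imputed freely, the four need not agree with one another.

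**The case against.** The strongest reply is that the text says what the model will include, not that nothing else enters, and that a condensed article leaves detail to an analysis plan that is not shown. That would answer a complaint about missing detail. It does not fully answer this one: the article goes down to single covariates and leaves out the one variable that the analysis estimates. Blinded analysts do not explain the omission, since a masked arm code can be used.

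Section 2.4 plans no formal efficacy testing and puts the standard deviation first; one check found that omitting arm moves the within-arm SD by only about 1% to 3%. This stands and lowers the severity. The planned complete-case analysis would show a discrepancy, but not that the imputation model caused it.

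A reader might infer more than the documents support:

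- That 20 iterations for 20 datasets leave no burn-in or spacing, so the draws are dependent. This assumes one chain with a draw kept at each iteration. The wording fits 20 separate chains of 20 iterations equally well, and both SAS and R are named.
- That the model has 1,224 parameters (48 + 48 × 49 / 2) and cannot be estimated. This assumes an unrestricted joint normal model, which is not stated. The large regression could be fitted at 15% missing; it failed only at 30%, twice the planned attrition. HOMA-IR and ISI are exactly collinear with FBG and FINS on the log scale, not on the raw scale.
- That imputation gains nothing over the mixed model. It can use diabetes duration, metformin dose and correlated outcomes that the mixed model ignores, so replacing it outright is a preference.

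**Conclusion.** The concern holds in this form: the stated imputation variables do not match the analysis, and the list is too long for the sample. At 15% attrition the effect estimate loses about 4% to 18% across the simulations, with 15% expected if drop-outs miss all follow-up and about 6% to 9% if they miss only Week 4. The direction, toward zero, does not depend on the pattern; the size does, and Section 2.4 gives no timing of drop-out. A loss of about 16% should therefore not be read as the general result: it belongs to the pattern in which every drop-out misses both follow-up visits.

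The result rests on assumed effects of 0.5 to 0.8 SD, a baseline to follow-up correlation of 0.5 and random drop-out. The rise in standard error from 0.25 to 0.44 is for one reading of the variable list, with auxiliaries unrelated to the outcome; informative auxiliaries would soften it. Every reading, 30 to 61 variables, is heavy for 60 participants.

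Severity: should be fixed. The rule is wrong as written, but the trial is a pilot without confirmatory testing.

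**What to change.** In Section 2.10, and in the analysis plan if there is one:

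1. Add randomised arm and arm × visit to the imputation model, or impute separately within arm. A masked arm code keeps the analysts blind.
2. Restrict the imputation model for each outcome to that outcome's own visits plus a few named covariates, such as age, sex and the baseline symptom score.
3. Impute FBG and FINS, then calculate HOMA-IR and ISI from them.
4. Report the likelihood-based mixed model on all observed data as a sensitivity analysis, alongside complete cases.

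The change costs wording and a small amount of programming. It needs no new data and no change to sample size or visits, and should be made before unblinding.

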### Randomization and blinding

2.5

Participants will be randomized 1:1 to taVNS group or sham control group, with stratification by age and gender to balance baseline characteristics between groups. The randomization sequence will be generated by an independent third-party biostatistician using SPSS 26.0, with group allocation sealed in sequentially numbered, opaque envelopes for strict allocation concealment. After baseline assessment, a dedicated study coordinator (fully blinded to group assignment) will open envelopes in numerical order to assign eligible participants.

Given the anatomical specificity of active and sham stimulation sites, intervention staff responsible for electrode placement and device operation cannot be blinded to group allocation. To mitigate potential bias, we have implemented pre-specified rigorous safeguards: The blinded coordinator exclusively manages group allocation, and only provides intervention staff with pre-marked anatomical diagrams of stimulation sites, with no disclosure of group identity at any time. Non-blinded intervention staff are strictly barred from outcome assessment, data entry, statistical analysis, or any communication with participants about group allocation or expected intervention effects. Both groups use identical stimulators with consistent nominal parameters; all intervention staff receive centralized standardized training to ensure identical operational execution and participant interaction across groups.

All outcome assessors, data analysts, biostatisticians, and participants will remain fully blinded to group allocation throughout the trial. Furthermore, treating physicians are solely responsible for routine clinical management and safety assessments; they have no access to group allocation and are strictly isolated from intervention implementation and outcome assessment. Participants will be informed that both interventions may induce a mild tingling sensation, and subjective feeling cannot be used to infer group assignment, to minimize anticipation bias. Outcome assessors will receive standardized training and regular inter-rater reliability checks to reduce measurement bias.

The effectiveness of the blinding will be formally assessed in Weeks 2 and 4 using the validated James Blinding Index (BI) method (James et al., 1996). The detailed statistical procedures for this assessment are outlined in the “Statistical Methods” section.

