To ensure ethical fairness, control-group participants who meet predefined criteria at study end may be offered compensatory taVNS treatment if clinically appropriate; this arrangement will be described in the informed consent form.

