**Figure 2 F2:**
[figure not shown]
Device and stimulation sites. Both groups used the HuaTuo SDZ-IIB device with identical parameters. Red dots indicate taVNS sites: CO7 (large intestine point) and CO13 (spleen point) in the cymba conchae. Blue dots indicate sham sites: SF2 (wrist point) and SF4 (shoulder point) in the scapha.

Stimulation site: auricular regions with high density of auricular branch vagus nerve (ABVN) fibers—specifically the cymba conchae and cavum conchae—targeting auricular “Large Intestine Point” (CO7) and “Spleen Point” (CO13) points as anatomical targets for modulation of gastrointestinal function.

Preparation: prior to each stimulation session, trained personnel will disinfect the skin, place and secure electrodes over the marked sites, and verify electrode impedance and device function.

Stimulation parameters: intermittent stimulation with an on/off cycle of 2 s on/3 s off; pulse width of 0.5 ms; frequency approximately 25 Hz; and current intensity individualized within the range 0.5–1.5 mA, titrated to achieve a mild tingling or warm sensation without pain. Intensity will be adjusted according to participant tolerance. This treatment protocol is based on a multicenter randomized controlled trial protocol validated for gastrointestinal disorders (Zhu et al., 2021; Shi et al., 2024; Yin, 2025). Furthermore, evidence from Molefi et al. (2025), which examined healthy subjects with visual-induced motion sickness and found that a 20 Hz frequency combined with a 0.2 ms pulse width did not significantly improve the composite gastrointestinal symptom score, further supporting the rationale for our choice of parameters.

Adverse sensations: if a participant experiences notable discomfort during stimulation, the intensity will be reduced or the session terminated and the event recorded as an adverse event (AE).

Detailed session duration and scheduling will follow the study protocol (see Figure 2 and the procedure manual), and all interventions will be administered by personnel trained in taVNS application.

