#### Treatment schedule and operational management

2.6.4

All participants will receive two stimulation sessions per day (morning and evening), each lasting 30 min, on 5 consecutive weekdays (Monday–Friday) for 2 consecutive weeks (total 10 sessions). During the initial treatment phase, the first three sessions will be administered and supervised in hospital outpatient or inpatient settings by trained study personnel; these sessions also serve as hands-on training for participants who will continue treatment at home. Thereafter, participants may complete remaining sessions at home according to the training protocol.

Home-based treatment requires daily completion of a treatment log documenting treatment time, device current intensity, local sensations, and any gastrointestinal symptoms. Study staff will review logs and confirm adherence weekly by telephone or via a secure remote platform, and will address participant queries. All interventions and any medication adjustments will be performed according to standard operating procedures (SOPs), recorded contemporaneously, and entered into the case report form (CRF).

Any deviation from the prescribed stimulation parameters or protocol procedures must be recorded with rationale. All staff administering or supervising treatments will be trained and certified according to the study training curriculum; competency assessments will be documented.

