#### Observation schedule and sample handling

2.6.5

The overall observation period is 5 weeks, comprising a 1-week baseline period (Week −1 to 0), a 2-week treatment period (Weeks 0–2), and a 2-week follow-up period (Weeks 2–4). Primary and key secondary outcomes (Metformin Symptom Severity Score, Bristol Stool Form Scale, and bowel urgency) as well as glycaemic/metabolic indices and selected inflammatory and mechanistic biomarkers will be assessed at baseline, Week 2, and Week 4. Selected biochemical markers will be repeated at baseline and either Week 2 or Week 4 according to the prespecified sampling schedule in the protocol appendix.

All biological specimen collection, processing, transport, and storage will follow a unified SOP. Blood samples will be drawn after an overnight fast unless otherwise specified, kept short-term at 4 °C, and transferred to long-term storage at −80 °C within the time limits defined in the SOP. Laboratory assay methods, quality-control procedures, and batch management are described in the trial appendix. The timeline of interventions, assessments, and visit windows is detailed in Table 1; adverse-event monitoring will be continuous throughout the entire study period.

**Table 1 T1:** Treatment and data collection.

Category	Study phase	Baseline	Visit 1	Visit 2
	Visit window	(Day 0)	Week 2	Week 4
Information collection	Basic medical history collection	×		
	Informed consent obtained	×		
	General demographics collection	×		
	Past medical and treatment history	×		
	Comorbidities and treatment history	×		
	Eligibility criteria check	×		
Primary outcomes	Metformin symptom severity score	×	×	×
Secondary outcomes	Bristol stool form scale	×	×	×
	Defecation urgency	×	×	×
	Quality of life scale	×	×	×
	FBG	×	×	×
	PG2h	×	×	×
	GA	×	×	
	IL-6, IL-10, TNF-α		×	
	GLP-1, BA, 5-HT, D-LA		×	
	ALT, AST, BUN, Cr (liver and renal function)		×	
Sample and data management	Adverse events (AEs) monitoring		×	×
	Sample collection record		×	
	CRF review by investigator (CRF-PI)	×	×	×
	CRF review by monitor (CRF-MON)	×	×	×
	Blinding assessment		×	×

“ × ” indicates that the corresponding assessment is performed at that visit. Baseline = day 0; visit 1 = week 2 (±3 days); visit 2 = week 4 (±3 days). All blood and stool specimens will be collected after an overnight fast.

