#### Primary efficacy outcome and assessment time points

2.7.2

The primary efficacy endpoint is the total score of the Metformin Symptom Severity Score, a validated, widely used self-report tool originally developed and psychometrically validated by McCreight et al. specifically for evaluating metformin-related gastrointestinal intolerance in adults with T2DM (McCreight et al., 2018).

In the original validation study by McCreight et al., this questionnaire demonstrated excellent reliability and validity: it showed strong internal consistency (Cronbach's α > 0.8), good test-retest reliability, and significant discriminant validity, with a highly significant difference in total scores between metformin-intolerant and metformin-tolerant patients (*P* < 0.0001) (McCreight et al., 2018). The questionnaire covers medication adherence, reasons for discontinuation, dose tolerance, gastrointestinal symptoms (nausea, abdominal bloating/pain, and diarrhea; frequency and subjective severity), changes in baseline symptoms, and an overall subjective tolerance rating, with a total score ranging from 0 to 50 points (0–10 = tolerable, 11–20 = mild intolerance, 21–30 = intolerable, 31–50 = severe intolerance). This questionnaire is used for the quantitative assessment of intolerance-related symptoms in this trial, not as a basis for clinical diagnosis.

Assessment time points include baseline, Week 2, and Week 4. Details of the questionnaire items and scoring criteria are provided in Table 2 (McCreight et al., 2018).

**Table 2 T2:** The metformin symptom severity score questionnaire.

No	Question	Option	Score
1	Are you still taking metformin?	Yes (skip to question 6)	0
		No	5
2	If you have stopped taking metformin, was it due to side effects?	Yes (continue to question 3)	5
		No (skip to question 6)	0
3	What dose were you taking at the time of discontinuing metformin?	500 mg once daily (1 tablet)	4
		1,000 mg once daily (2 tablets)	3
		500 mg twice daily (2 tablets)	2
		2,000 mg once daily (4 tablets)	1
		1,000 mg twice daily (2 tablets)	0
4	Have you ever taken a lower dose of metformin and tolerated it well?	Yes	0
		No	1
	If yes, what was the maximum dose you tolerated?	(e.g., 500 mg once daily)	2
5	Have you been trialed on a modified release preparation of metformin (e.g. Glucophage SR)?	Yes	2
		No	0
In the last week of taking metformin, have you experienced?			
6	Nausea?	Yes	1
		No	0
	If yes, how often?	More than once a day	4
		Once a day	3
		Occasionally	2

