Complete case analysis will be conducted as a sensitivity analysis to verify the robustness of the core findings. Exploratory subgroup analyses stratified by age, sex, and diabetes duration are descriptive only.

The success of blinding will be evaluated using the James BI for all participants and independent outcome assessors at Week 2 and Week 4. The BI is scaled from 0 (all participants guessed correctly) to 1 (all participants guessed incorrectly), with 0.5 indicating completely random guesses (the standard for successful blinding). Weights are assigned consistent with the original James method: 0.00 for correct guesses, 1.00 for incorrect guesses, and 0.50 for uncertain/unable to judge responses, with uncertain responses split equally between correct and incorrect guesses. The BI and its 95% CI will be calculated using the jack-knife procedure recommended in the original method (James et al., 1996).

Safety parameters (CBC, ALT, AST, urea, creatinine) are analyzed similarly, comparing abnormality rates. All tests are two-sided with α = 0.05; effect sizes are reported with 95% CI.

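### Blinding guesses are taken only at Weeks 2 and 4 and without a reason, so an index below 0.5 could not separate symptom benefit from a blind lost through the ear site

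*Protocol article*

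**What the plan says.** Section 2.5 (Randomization and blinding) states: "The effectiveness of the blinding will be formally assessed in Weeks 2 and 4 using the validated James Blinding Index (BI) method". Section 2.10 (Statistical methods) repeats the timing: "The success of blinding will be evaluated using the James BI for all participants and independent outcome assessors at Week 2 and Week 4". Table 1 marks the blinding assessment at the same two visits. Section 2.10 scores the index from 0 (all guesses correct) to 1 (all incorrect) and treats 0.5 as the standard for successful blinding. Uncertain answers carry weight 0.5.

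Section 2.6.5 sets out "a 2-week treatment period (Weeks 0–2), and a 2-week follow-up period (Weeks 2–4"), so the first guess falls at the end of treatment. Section 2.7.2 describes the primary score as "a validated, widely used self-report tool originally developed and psychometrically validated" and adds: "Assessment time points include baseline, Week 2, and Week 4". Both blinding visits are therefore also the post-baseline visits for the primary score.

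Section 2.6.3 makes the stimulation site the only intended difference between arms. The Figure 2 caption reads "Red dots indicate taVNS sites: CO7 (large intestine point) and CO13 (spleen point) in the cymba conchae"; the sham points lie in the scapha. Section 2.6.4 has the first three sessions supervised and used as training, then: "Thereafter, participants may complete remaining sessions at home according to the training protocol". The one message to participants described in section 2.5 concerns tingling, not site.

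**The concern.** The participant rates the primary outcome, so the participant's blind is the one that protects it. Keeping assessors, analysts and physicians blinded does not. A participant who self-treats must know and handle the site, which is the one feature that differs between arms.

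The planned check has to show whether that blind held. By Week 2, however, a participant may guess from symptom change rather than from anything about the procedure. With no guess before most of the treatment and no stated reason, an index below 0.5 would be ambiguous: the treatment may have worked with the blind intact, or the blind may have failed.

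The stake is what the pilot can pass on. It is meant to inform a definitive trial, and whether this sham remains credible with home use is among the things that trial would need to know.

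**Working it through.** **Inputs from the protocol**

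- Evaluable sample (section 2.4): 30 × (1 − 0.15) = 25.5, stated as 25 per group; degrees of freedom 2 × 25 − 2 = 48. Both stated figures reproduce. I use n = 50 for the index.
- Sessions (section 2.6.4): two a day, five days a week, two weeks gives 2 × 5 × 2 = 20, but the section gives a total of 10.
- Largest possible home share: (20 − 3)/20 = 85%, or (10 − 3)/10 = 70%. These are maxima, since home use is optional.
- Index (section 2.10): mean weight, with 0 for correct, 1 for incorrect and 0.5 for uncertain.

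**Assumed inputs**

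The protocol gives no response rates. Let a be the proportion improving on taVNS and s the proportion improving on sham. The arms are equal in size.

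**Cause A: site fully masked, each guess follows improvement, nobody uncertain**

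- Proportion correct = 0.5a + 0.5(1 − s).
- Index = 1 − proportion correct.
- SE = √[index × (1 − index)/50].

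For a = 0.60 and s = 0.30:

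- Proportion correct = 0.30 + 0.35 = 0.65, so the index is 0.35.
- SE = √(0.35 × 0.65/50) = 0.067.
- 95% CI = 0.35 ± 1.96 × 0.067, or 0.22 to 0.48.

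**Cause B: no benefit, a share u knows the arm from the site, the rest guess at random**

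- Proportion correct = u + (1 − u)/2, so the index = (1 − u)/2.
- An index of 0.35 needs u = 1 − 2 × 0.35 = 0.30.

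**Range over assumed response rates**

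| Response, taVNS / sham | Index under A | 95% CI | Share unblinded giving the same index under B |
|---|---|---|---|
| 50% / 50% | 0.50 | 0.36 to 0.64 | 0% |
| 50% / 30% | 0.40 | 0.26 to 0.54 | 20% |
| 60% / 30% | 0.35 | 0.22 to 0.48 | 30% |
| 70% / 30% | 0.30 | 0.17 to 0.43 | 40% |
| 70% / 20% | 0.25 | 0.13 to 0.37 | 50% |

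**With 30% uncertain answers, 60% / 30% response**

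- Correct: 0.70 × 0.65 = 0.455. Incorrect: 0.70 × 0.35 = 0.245.
- Index = 0.245 + 0.30 × 0.5 = 0.395.
- Variance = [0.455 × 0.395² + 0.245 × 0.605² + 0.30 × 0.105²]/50 = 0.00328, so SE = 0.057.
- 95% CI = 0.28 to 0.51.

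The intervals use a normal approximation, whereas the plan uses a jack-knife. The match between A and B is in the point value, so it does not depend on the interval method.

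**The case against.** Much of the opposing case stands.

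- **Knowing one's site is not knowing one's arm.** Section 2.5 says staff cannot be blinded, and a reader might infer that self-treating participants cannot be either. Staff, however, know both sites and what they mean. A participant sees one site, feels tingling in either arm from the same device model, and has no stated way to tell which site is active.
- **Point names.** A reader might infer from Figure 2 that participants learn they are treated at a bowel or a wrist point. Nothing says so. Staff are also barred from discussing expected effects, and the training material and procedure manual are not shown.
- **Response by Week 2.** It is tempting to say that symptoms will already have responded. The protocol shows only that treatment ends then. Metformin is titrated weekly over the same period, so improvement cannot be presumed.
- **Size.** It would overstate the arithmetic to say that the index would exclude 0.5 under a perfect blind. It does at 60% / 30% with no uncertain answers. It does not at 50% / 30%, nor at 60% / 30% with 30% uncertain.
- **Compensatory treatment.** Section 2.6.1 says "control-group participants who meet predefined criteria at study end may be offered compensatory taVNS treatment if clinically appropriate". A reader might infer unblinding while others are still in treatment. That needs one particular reading of study end, which the section does not define. Even on that reading, the person concerned has finished outcome collection and others do not learn their own arm.
- **Stakes.** This is a pilot with no formal efficacy test planned in section 2.4, no decision rule is tied to the index, and the Discussion already concedes expectation bias.

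A guess taken before home use also cannot detect blinding lost at home, so it cannot replace the later checks. What the objection leaves untouched is that both guesses coincide with the symptom score and that no reason is described for either.

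**Conclusion.** The point holds as a weakness in a stated design choice, not as evidence that the blind will fail. The assessment times are fixed consistently in sections 2.5 and 2.10 and Table 1, so this is not a detail lost in condensing the article. At those times, with an index judged against 0.5 and no reason recorded, real benefit and site-based unblinding can give the same value: 0.35 under 60% / 30% response, with a range of 0.40 to 0.25 over the other unequal rates tried.

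This rests on assumed response rates and on guesses that follow improvement. It disappears if the arms respond equally, but a difference between arms is the effect the trial looks for. The consequence is limited: the pilot loses a clear reading on whether the sham is credible with home use. It is a cheap improvement worth making before recruitment or by early amendment.

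**What to change.** 1. In sections 2.5 and 2.10 and Table 1, add a participant guess at the end of the third supervised session, with certainty and main reason (site, sensation, symptom change, other). This comes after 3 of 20 sessions (15%), or 3 of 10 (30%), and so before most of the treatment.
2. Keep the Week 2 and Week 4 guesses, since only they can capture blinding lost during home use. Add the same certainty and reason items to them.
3. Report all guesses by arm and by reason, beside the overall index.
4. As a supporting step, use neutral site codes without organ names in training sheets, diagrams and logs that participants see, if this is not already done.
5. Reconcile two places: the session total in section 2.6.4 with its own schedule, and study end in section 2.6.1 with the statement in section 2.5 that blinding lasts throughout the trial.

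The cost is one short set of questions at a session that is already supervised, two added items at existing visits, and some relabelling. The downside is that an early question may prompt some participants to think about allocation. Eligibility, treatment and sample size are unaffected.
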